### Public and patient involvement (PPI)

PPI has featured in every step of the research process. The research team has consulted caregivers using one-to-one interviews and focus groups to clarify the study aims and rationale. These consultations confirmed the absence of support for caregivers and their enthusiasm for writing as a potential intervention. Caregivers reported that writing interventions, like Positive Written Disclosure, could be beneficial as they address: (1) caregivers’ limited opportunities to express themselves, (2) limited availability and ability to physically attend carer support groups, and (3) the increased burden that can come from providing peer support within carer support groups.

The C4C LEAP has also been involved in designing this study. Specifically, they identified alternative approaches to recruitment (e.g. involving more third sector organisations), assisted in selecting the trial outcome measures, and selected the images that will be used in the WC group. Most significantly, the C4C LEAP identified that the act of writing, irrespective of the topic, could be therapeutic—and they subsequently proposed the inclusion of the NWC group. All of the study materials were reviewed by the C4C LEAP to ensure they were clear and accessible. The involvement of the McPin Foundation, a specialist mental health research charity that champions expertise from experience in studies, has also supported the structural development of PPI within the study.

The C4C LEAP will continue to be part of the study. Their role will be to monitor and advise on recruitment (including problem solving), support qualitative data analysis, and assist in the interpretation of the study results. At the point of dissemination, they will be involved in planning activities.

### Research governance

We have produced this protocol in line with the Standard Protocol Items: Recommendations for Interventional Trials (SPIRIT) guidelines [48] (see Additional files 1, 2 and 3). This study is funded by the Dunhill Medical Trust (R431/0715) and sponsored by the University of Sussex (BSMS/16/010/JON). Local governance approval was granted by Sussex Partnership NHS Foundation Trust. Ethical approval was granted by the North-West Lancaster Research Ethics Committee on 24/11/2016 (REC reference: 16/NW/0757).

This pilot trial will be monitored by a Trial Steering Committee, with an independent chair, and including academic, clinical, trial management, and lived experience experts, in accordance with the Medical Research Council (MRC) [49] guidelines. The trial will also be monitored by a separate Lived Experience Advisory Panel (C4C LEAP).

Adverse events and issues of risk will be addressed in line with the National Institute for Health Research Good Clinical Practice guidelines. If any adverse events occurring during the study are deemed to be severe and related to the study, then this may result in the early termination of the trial—this decision will be made by the study sponsors and Trial Steering Committee. All adverse events, whether they are related to the study or not, will be reported in the final study report.

### Dissemination

We plan to disseminate the results of this study to both academic and non-academic communities. The results will be written up for publication in a peer-reviewed academic journal, using open access routes wherever possible. Additionally, all participants that request one will receive a lay summary of the study findings. We also plan to disseminate the findings via relevant third sector organisations, events, and publications, such as carers’ centres, Rethink Mental Illness, and the McPin Foundation.

## Discussion

The results of this pilot RCT will determine whether Positive Written Disclosure is an acceptable intervention for older adult caregivers of people experiencing psychosis symptoms. The exit interviews, recruitment and retention rates, and the effect sizes of the co-primary and secondary outcomes will all be used to determine whether a definitive trial of PWD in this population is justified and feasible. If the results of this trial are promising then, with the support of the C4C LEAP, the qualitative and quantitative results can be used to refine the intervention and study protocols.

If PWD is found to be effective within a definitive trial, then this intervention has the potential to improve the wellbeing of a group of people currently neglected by healthcare services. Furthermore, the self-directed nature of PWD would mean this intervention could be implemented without incurring any significant healthcare costs.

Trial status: The trial opened for recruitment in January 2017.

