The aims of the pilot trial are to (1) determine whether a definitive trial of PWD on older adult caregivers of people experiencing psychosis is justified in terms of recruitment, retention, reasons for dropout, and adherence to writing task; (2) estimate the pooled standard deviation for the primary outcome (mood) to be used for future sample size calculations in the event of a definitive trial being justified and gain insight into what an appropriate Minimal Clinically Important Difference (MCID) might be for future studies; and (3) identify whether PWD and the study design is acceptable, accessible, and feasible to participants by using a combination of questionnaires, recruitment and retention rates (quantitative), and post-study interviews (qualitative), all supported by a patient and public involvement reference group.

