We will also collect data on the Toronto Alexithymia Scale (TAS 20) [38]. This questionnaire measures trait alexithymia (the ability to identify emotions). As alexithymia is considered a trait characteristic, we will only administer this measure at baseline (T0). The questionnaire has three sub-scales: difficulty describing feelings, difficulty identifying feelings, and externally orientated thinking. These sub-scales are comprised of five, seven, and eight items respectively. The questionnaire has 20 items in total. The scale has good internal consistency (Cronbach’s *α* > .70) [39]. This measure will be entered as a moderator on the primary outcome within the definitive trial, in line with recent research findings that PWD is more effective for those low in alexithymia [24].

We will collect the participants’ demographic information. As part of this, we will collect data on the number of sick days (i.e. days when unable to work or complete usual daily activities because of health) and GP visits that participants have experienced at each time point. This data can then be used to measure healthcare utilisation. We will measure quality of life using the ED-5D-5L health questionnaire [40]. This measure has five items and one visual analogue scale. An index score can also be computed for use within health economics. The measure has strong internal consistency (Cronbach’s *α* = .85) [41].

For participants that are allocated to one of the writing conditions (either PWD or WC), we will ask participants to note down the time they start and finish writing each day so that we can determine whether participants adhered to the writing task instructions. Also, all writing excerpts will be assessed using the Linguistic Inquiry and Word Count (LIWC) [42]; this computer software will measure the frequency of different word classes, as well as the total number of words used. The results of the LIWC will be used to assess the validity of our manipulation, i.e. those in the PWD condition should use more positive emotion words than the WC group.

The primary outcome and secondary outcomes 1 to 4 will be collected at baseline (T0) and 1 (T1), 3 (T2), and 6 (T3) months post baseline. The primary comparison across all outcomes will be PWD versus the WC. Assessments will be completed at a location that is convenient for the participant; all participants will be offered home visits.

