### Planned analysis

The data analysis will be conducted by the trial statistician (SB). The findings of this trial will be reported in line with the CONSORT guidelines for pilot RCTs, including a PRISMA diagram as in Fig. 1. Recruitment rates will also be expressed as a percentage, reflecting the number of participants who gave consent to take part in this study relative to the total number of people who were approached to participate. Participant retention in the study at each of the assessment time points will be reported as a percentage. Wherever possible, the reason for study and intervention dropout will be recorded—this may not be possible for all cases where participants dropout from the study, as each participant reserves the right to withdraw from the study without giving any reason.

Adherence to the writing tasks (only relevant for the PWD and WC groups) will be determined by the number of writing extracts completed (should be 3), the self-reported times that participants started and finished writing (should amount to 20 min per day), and the results of the Linguistic Inquiry and Word Count (LIWC) software [42]. Comparison of the LIWC data should show that those in the PWD group and the WC group write similar numbers of words over the 3 days but that the trend will be for the PWD group to use more positive words than the WC.

As this is a pilot study, analyses will be descriptive, and statistical comparison between groups will not be made, but rather, data for each group will be presented separately in a table side by side, with 95% confidence intervals [44]. The amount of complete data for the primary outcome across all time points will be expressed as a percentage.

To our knowledge, there is no recommended Minimal Clinically Important Difference (MCID) for our primary outcome, the PANAS [30]. Therefore, one of the aims of this study is to suggest an MCID for use in future studies. This estimation will be based on the guidance of Copay et al. [45]: as the MCID is assumed to reflect a small effect size, the baseline standard deviation across the whole sample will be multiplied by 0.2 (this value represents a small effect size, as recommended by Cohen [46]).

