The exit interviews with participants in the PWD and WC groups will be transcribed, removing all identifiable information. Where necessary, pseudonyms will be used. The transcripts from each interview will be analysed within QSR NVivo 11, using thematic analysis (TA) [47]. The analysis will involve research team members and the C4C LEAP. Once familiar with the content of the transcripts, we will generate initial codes that stay close to the data. These codes will be semantically clustered into sub-themes, and finally, these sub-themes will be clustered into main themes. The final thematic structure will be described and supported with illustrative quotes from the interviews. The use of TA will enable us to identify patterns of meaning within and across participants. If a definitive trial is justified, these qualitative results will be instrumental in refining the study protocol.

A definitive trial will be justified if (1) the primary outcome measure is at least 80% complete, (2) attrition is no greater than 40% by T3, and (3) the trial and intervention are considered acceptable and accessible by patients.

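### The Discussion makes outcome effect sizes an input to the decision on a definitive trial; the progression criteria and aim 1 contain no such input, and the pilot is too small to support it

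*Protocol article*

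**What the plan says.** The main-text Discussion lists the grounds for going on to a definitive trial. Beside the exit interviews and the recruitment and retention rates, it says that "the effect sizes of the co-primary and secondary outcomes will all be used to determine whether a definitive trial of PWD" is justified and feasible. That sentence gives no contrast, follow-up visit, threshold or weight.

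Other sections describe the decision differently:

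- **Planned analysis, progression criteria.** There are three conditions, of which the first reads "A definitive trial will be justified if (1) the primary outcome measure is at least 80% complete". The second caps loss of participants at 40% by the 6-month visit. The third requires that those taking part find both trial and intervention acceptable and accessible.
- **Background, aim 1.** The question is whether a definitive trial "is justified in terms of recruitment, retention, reasons for dropout, and adherence to writing task". Aim 2 adds a pooled SD and insight into an MCID, but no treatment effect.
- **Planned analysis, method.** "As this is a pilot study, analyses will be descriptive, and statistical comparison between groups will not be made"; each arm is tabulated beside the others with 95% intervals.
- **Measures.** "The primary comparison across all outcomes will be PWD versus the WC". The text does not say whether this refers to the pilot or to the definitive trial.

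**The concern.** The go/no-go decision is the main product of this pilot, and the article states two rules for it. Suppose completeness, attrition and acceptability all meet their criteria, but the PANAS effect sizes favour the writing control. Planned analysis says that a definitive trial is justified. The Discussion lets the effect sizes count against it. The reverse case, in which a favourable effect size is used to excuse a missed criterion, is equally open.

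The added input is also one that the pilot was not sized to estimate. The sample size rests on a pilot rule of thumb plus attrition, not on the precision of a difference. An unreliable estimate could help to stop a worthwhile intervention or to carry an ineffective one forward. With two co-primary scales, several secondary outcomes, three follow-ups and no stated visit or threshold, the team could also decide after seeing the data which effect sizes matter.

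**Working it through.** **1. The plan's own figure.** Under Participants, the target is 12 per arm allowing for up to 40% attrition: 12 / (1 − 0.40) = 20 per arm, and 3 × 20 = 60. This reproduces exactly. The number available for a PWD-WC difference therefore lies between 20 per arm (no loss) and 12 per arm (the largest loss allowed for).

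**2. The passages side by side.** Each of the other inputs in the Discussion sentence has a counterpart elsewhere. Interviews bear on the acceptability criterion, retention on the attrition criterion, and recruitment is in aim 1. Effect sizes are the only input with no counterpart in either the three criteria or aim 1.

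**3. Precision of that input.** Inputs:

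- n = 20 or 12 per arm (Participants).
- Contrast PWD versus WC (Measures).
- Benchmark 0.2 SD, the MCID proposed for the PANAS under Planned analysis.
- Assumptions: equal arms, normal approximation, no baseline adjustment.

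Formulas, in SD units:

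- SE = √(2/n)
- 95% half-width = t(0.975; 2n − 2) × SE
- Probability of the wrong sign when the true effect is 0.2 = Φ(−0.2 / SE)

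| n per arm | SE | 95% half-width | Half-width / 0.2 | Wrong sign at true 0.2 SD |
|---|---|---|---|---|
| 20 | √(2/20) = 0.316 | 2.024 × 0.316 = 0.64 | 3.2 | Φ(−0.632) = 0.264 |
| 12 | √(2/12) = 0.408 | 2.074 × 0.408 = 0.85 | 4.2 | Φ(−0.490) = 0.312 |

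By symmetry, if the true effect is zero, one scale at one visit shows an apparent benefit of 0.2 SD or more with the same probabilities, 0.264 and 0.312. Using 0.2 SD as a cut-off here is an illustration; the protocol does not set it as a go rule.

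**4. Does baseline adjustment rescue it?** Adjustment multiplies the SE by √(1 − r²), where r is the correlation between baseline and follow-up. The documents give no r, so a range of 0.5 to 0.7 is assumed: the factor is 0.866 at r = 0.5 and 0.714 at r = 0.7.

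| n per arm | r | Half-width | Wrong sign at true 0.2 SD |
|---|---|---|---|
| 20 | 0.5 | 0.640 × 0.866 = 0.55 | Φ(−0.2/0.274) = 0.23 |
| 20 | 0.7 | 0.640 × 0.714 = 0.46 | Φ(−0.2/0.226) = 0.19 |
| 12 | 0.5 | 0.847 × 0.866 = 0.73 | Φ(−0.2/0.354) = 0.29 |
| 12 | 0.7 | 0.847 × 0.714 = 0.60 | Φ(−0.2/0.292) = 0.25 |

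The estimate improves, but the half-width is still more than twice the MCID in the best of these cases (0.46 / 0.2 = 2.3).

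**5. More than one outcome.** If there is no true effect, the chance that at least one of the two co-primary scales shows 0.2 SD or more in favour of PWD at a given visit was simulated, with assumed correlations between the two estimates of 0.5 and 0. It is 0.40 to 0.46 at 20 per arm and 0.46 to 0.53 at 12 per arm.

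**The case against.** The best defence is that this is one summary sentence in an article's Discussion. The operative rule stands in Planned analysis, agrees with aim 1, and is not altered by loose wording later. Nothing in randomisation, data collection, sample size or the planned tables depends on the sentence. This bears on severity, but it does not remove the conflict: the sentence says how the decision will be made, and a steering committee or funder could rely on it.

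Three stronger readings are tempting, and the documents do not support them.

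- *The decision as a whole would be mostly noise.* The calculations concern the effect-size input only. Interviews, recruitment and retention also enter, and no weights are given, so the effect on the whole decision cannot be worked out.
- *The planned analysis forbids or cannot produce a between-group effect size.* Planned analysis says that "analyses will be descriptive, and statistical comparison between groups will not be made", which most naturally means no hypothesis testing. Arm means with intervals and arm sizes allow a descriptive difference to be derived, and a pooled SD is planned for the primary outcome. The fit with the Discussion is poor, but the clear contradiction is with the criteria and aim 1.
- *The definitive trial would be mis-sized from the observed effect.* The stated planning inputs are the pooled SD and an MCID of 0.2 times the baseline SD. Nothing uses the observed treatment effect as a target difference.

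Two further points stand in part. The term could mean within-group change, but that would be uncontrolled and is equally absent from the criteria. Measures does name PWD versus WC as the primary comparison, so the contrast is not wholly open, although visit, threshold and weight are. The 12-per-arm figures are the worst case that the plan allows for and should not be read as typical of the earlier visits.

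**Conclusion.** The concern holds as an inconsistency in the progression rule that should be fixed. The Discussion adds a decision input that the three criteria and aim 1 do not contain and leaves it undefined. For the PWD-WC contrast, that input has a 95% half-width of about 0.64 to 0.85 SD against a 0.2 SD MCID. At a true effect of 0.2 SD it would have the wrong sign in about 26% to 31% of pilots unadjusted, and about 19% to 29% adjusted.

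The contradiction rests on the text alone. The figures rest on equal arms of 12 to 20, a normal approximation and, for the adjusted range, an assumed correlation of 0.5 to 0.7. They show that this one input cannot support a go or a no-go; they do not measure the reliability of the decision as a whole.

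**What to change.** In the Discussion, delete effect sizes from the sentence on how the decision is made. State that progression rests on the three feasibility criteria under Planned analysis, consistent with aim 1. If a PWD-WC difference is shown, report it with its 95% interval, label it descriptive, and say that it is not used for progression.

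The cost is one sentence of wording. The sample size, data collection and planned tables are unchanged. The change should be made before outcome data are seen, so that there is no choice between two rules afterwards.

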## Abbreviations

C4C: Caring for Caregivers
CRF: Case Report Forms
CWSv2: Caregiver Wellbeing and Support Scale
DASS-21: Depression Anxiety and Stress Scale
GP: General practitioner
GSES: General Self-Efficacy Scale
LEAP: Lived Experience Advisory Panel
LIWC: Linguistic Inquiry and Word Count
LTS: Leisure Time Satisfaction
MCID: Minimally Clinically Important Difference
MRC: Medical Research Council
NHS: National Health Service
NWC: Non-Writing Control group
PANAS: Positive and Negative Affect Scale
PPI: Public and patient involvement
PWD: Positive Written Disclosure
RCT: Randomised controlled trial
SPIRIT: Standard Protocol Items: Recommendations for Interventional Trials
TA: Thematic analysis
TAS: Toronto Alexithymia Scale
VAS: Visual analogue scales
WC: Writing Control task
WED: Written Emotional Disclosure
